#### Presentations

The DMW and HEDIS presentations present the content summarized in Table 1 utilizing high quality graphic material recently awarded The Communicators Award of Excellence in an international competition.

**Table 1 T1:** Presentation Schematic

Sequence of Initial Activities	VB Presentation	UC Presentation
PRESENTATION	Prevalence in the workplace	Prevalence in society

	Depression burden to	
	Employer	Depression burden to individual
	Employee	

	Problems treating depression in usual care	Problems treating depression in usual care

	DMW as an indicator of high quality care	HEDIS as an indicator of high quality care

	Clinical effectiveness of DMW Care Organizational effectiveness of DMW	Obtaining HEDIS indicators for outpatient depression management

	DMW Calculator	Interpreting HEDIS indicators for outpatient depression management

	Description of Technical Assistance	Description of Technical Assistance

DISCUSSION	Open discussion of value of DMW Care	Open discussion of value of HEDIS quality care

#### DMW presentation

The two-hour DMW presentation educates employer representatives about DMW Care and its evidence-based impact on clinical and work outcomes. Employer representatives receive a company-specific return on investment (ROI) estimate associated with DMW Care. As shown in Table 2, this estimate is generated by a calculator the research team developed in its earlier studies by translating scientifically derived estimates of DMW Care's impact on absenteeism and productivity at work to a monetized savings in lost work days, varying pertinent employee, organizational, and vendor characteristics [25]. During the presentation, employers are encouraged to explore purchasing a depression product for their company and to request free technical assistance to help them purchase a DMW Care quality product.

**Table 2 T2:** Calculator Schematic

Major Constructs	Definition
Size ^1^	Number of non-unionized domestic employees currently receiving health care benefits

Industry ^1,3^	Industry type allows calculator to estimate age by gender employee distributions to calculate depression prevalence

Hourly wage/fringe ^1,3,4^	Hourly wage plus BLS-estimated fringe for non-supervisory personnel in industry type

Missed work policies^1^	Paid sick leave policies
	Temporary employee policies
	Work makeup policies and practices

Depression in workforce^2,3^	Number of employees in workforce with 1-year major depression and/or dysthymia

Lost work days associated with Depression^2,3^	Workdays an employer pays for where work is never completed by temporary, coworkers or depressed worker when s/he feels better

DMW employee participation rate ^2,3,4^	Number of depressed employees expected to participate in DMW each year

DMW cost per employee participant^2,3,4^	Estimate cost per employee participant

Annual DMW impact on lost work days ^2,3^	Incremental reduction in lost work days in workforce using DMW employee participation estimate

Other potential payers ^2,3^	Summary of peer-reviewed literature on economic impact on health plans and employees

Performance standards ^2,3^	DMW key component operationalization

Annual DMW cost ^2,3^	Based on estimated participation rate and cost per employee participant

Annual DMW cost per reduced lost work day ("ROI") ^2,3^	DMW cost/incremental reduction in lost work days

^1^indicates user provides information.

^2^indicates calculator provides information.

^3^indicates calculator provides documentation/detailed description of estimate derivation and graph.

^4^indicates user can modify default values.

#### HEDIS presentation

The two-hour HEDIS presentation educates employers about HEDIS indicators for antidepressant medication management and their use in monitoring outpatient depression treatment quality. Employers receive HEDIS indicators for antidepressant medication management for their most subscribed plan if that plan reports its HEDIS scores to the National Committee for Quality Assurance; otherwise, they receive the HEDIS indicators for other plans in the area. During the presentation, employers are asked to encourage their most subscribed health plan to improve its HEDIS indicators for depression (or to calculate its HEDIS indicators if it does not report them). In addition, employers are encouraged to ask their plans to provide individual feedback to clinicians about the quality of their depression care, provide greater formulary access to newer depression drugs, and require lower copayments for outpatient mental healthcare. While causal evidence is lacking, a study reports that these plan characteristics are associated with better HEDIS indicators for antidepressant medication management [26]. Because previous studies indicate that the HEDIS presentation will have little to no impact on employer purchasing [27-31], depression product purchasing rates in the UC condition capture vendor efforts to market depression products to employers in both conditions during follow-up.

The second author [name] provides presentations to both groups. DMW and HEDIS presentation sessions are scheduled for the same day in random order, one in the morning and the other in the afternoon. If after agreeing to be in the study, employer representatives fail to attend the meeting, they are asked to schedule a time in the next four weeks to complete the presentation and data collection individually. If they cannot do so, they are dropped from the study.

#### Technical assistance (TA)

TA is the provision of individualized consultation to enable employers to improve the depression care their employees receive. When an employer representative requests TA, the TA consultant schedules a two-hour phone call to conduct the initial consultation followed by a second call approximately one month later. In the VB condition, the TA assists employer representatives in building broad support within their organization for the purchase, in identifying DMW vendors, and in developing contracts for the program. In the UC condition, the TA consultant assists employer representatives to work with their most subscribed health plan to improve the depression treatment they deliver as measured by their outpatient antidepressant management HEDIS indicators, and/or to provide individual feedback to clinicians about the quality of their depression care, provide greater formulary access to newer depression drugs, and require lower copayments for outpatient mental healthcare.

#### Data collection

All employer representatives are asked to complete the pre-presentation survey immediately before the presentation begins, the post-presentation survey immediately after the presentation ends, as well as a 12- and 24-month follow-up survey. Twenty-four-month follow-up surveys are projected to be completed by September 2013. Employers are paid $100 for completing the pre- and post-presentation survey, $100 for completing the 12-month survey, $100 for completing the 24-month survey, and an additional $50 for completing all surveys. Pre- and post-presentation data are collected in the room in which the presentations are delivered using laptop computers. Twelve- and 24-month follow-up data are collected in the subject's office or home using the web. The research team member who actively contacts employers who do not respond to a standardized electronic cue to complete follow-ups is blinded to condition. Pre-presentation data (descriptive characteristics, mediating, moderating, and outcome variables) are collected from employer representatives immediately before the presentation. Post-presentation data (mediating variables and presentation evaluation) are collected from employer representatives immediately after the presentation. Twelve and 24-month data (mediating, selected moderating and outcome variables) are collected in a three month window of the expected timeframe. Employers whose representatives are no longer in the position or with the company are asked to nominate another representative to complete the presentation and remaining follow-up interviews.

The research team also conducts semi-structured interviews with Executive Directors of each participating coalition at baseline (two weeks before the presentation) and at 24-month follow-up. Executive Director baseline interviews provide qualitative data about coalition efforts to encourage VB purchasing. Executive Director follow-up interviews are designed to provide qualitative data on intervention impacts that may not be observable in the structured interviews we conducted with employers, as well as solicit insights from Executive Directors about VB intervention impact and strengthening. Instrumentation is available on the project's website [32].

#### Construct Measurement

Employer benefit purchasing behavior (EBPB) over the previous 12 months will be measured at 12 and 24 months as an ordinal variable with four levels: product exposure (*e.g*., presentation participation) only; product exposure and discussion with decision-maker only; product exposure, discussion with decision-maker and product pursuit; and product exposure, discussion with decision making, product pursuit, and product purchase. Planned secondary analyses will examine intervention impact on product purchase defined as a dichotomous variable. Descriptive, moderating, and mediating variables will be defined in subsequent manuscripts testing the study's hypotheses.

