**Methods:**

In a randomized controlled trial conducted with 360 employers of 30 regional business coalitions, the research team proposes to compare the impact of a value-based marketing intervention to usual-care marketing on employer purchase of depression products. The study will also identify mediators and organizational-level moderators of intervention impact. Employers randomized to the value-based condition receive a presentation encouraging them to purchase depression products scientifically shown to benefit the employee and the employer. Employers randomized to the usual-care condition receive a presentation encouraging them to monitor and improve quality indicators for outpatient depression treatment. Because previous research demonstrates that the usual-care intervention will have little to no impact on employer purchasing, depression product purchasing rates in the usual-care condition capture vendor efforts to market depression products to employers in both conditions while the value-based intervention is being conducted. Employers in both conditions are also provided free technical assistance to undertake the actions each presentation encourages. The research team will use intent-to-treat models of all available data to evaluate intervention impact on the purchase of depression products using a cumulative incidence analysis of 12- and 24-month data.

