#### Data Analysis

The research team will test the experimental hypothesis using an intent-to-treat model of all available data, conducting a cumulative incidence analysis over 24 months. Assuming 20% dropout at 24 months (remaining n = 144/group), the post-attrition sample will provide 86% power to find a 0.35 effect size on the EBPB scale using a two-tailed test with p < 0.05.

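### A fixed 12-month look-back at each follow-up survey does not cover the full 24 months when the 12-month survey is late or missed, or when the surveys are more than 12 months apart

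*Protocol article*

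**What the plan says.** The section Construct Measurement defines the outcome and its recall period together: "Employer benefit purchasing behavior (EBPB) over the previous 12 months will be measured at 12 and 24 months as an ordinal variable". The scale has four levels, from exposure alone up to purchase. Purchase by itself is secondary: "Planned secondary analyses will examine intervention impact on product purchase defined as a dichotomous variable".

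The section Data collection says that the 12- and 24-month data "are collected in a three month window of the expected timeframe". It pays for each follow-up survey separately, with a bonus for completing all of them, and provides for active contact of employers who do not respond. Employers whose representative has left "are asked to nominate another representative to complete the presentation and remaining follow-up interviews".

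The section Data Analysis tests the experimental hypothesis "using an intent-to-treat model of all available data, conducting a cumulative incidence analysis over 24 months". The abstract names the source of that analysis: "using a cumulative incidence analysis of 12- and 24-month data".

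Nothing in the article extends the recall back to the presentation or to the last completed survey, asks for a purchase date, or names a second source of employer purchase data. The interview with coalition Executive Directors at 24 months is described as qualitative.

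**The concern.** A cumulative incidence from presentation to month 24 needs every month of that interval to be asked about at least once. Two look-backs of 12 months do this only if the surveys fall at the right times, and the protocol's own window allows other times.

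Time that no survey asks about cannot be recovered in the analysis. A purchase, or an early discussion or pursuit of a product, that falls in the gap is invisible. The ordinal primary outcome is therefore exposed as well as the purchase endpoint. If the employer is still treated as observed for the whole period, the count in that arm is too low and the difference between value-based (VB) and usual-care (UC) marketing shrinks.

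**Working it through.** **1. The plan's own power figure.** Inputs from Data Analysis: 144 per group, effect size 0.35, two-sided 5%.
- Sample: 360 × 0.80 / 2 = 144.
- Power: 0.35 / √(2/144) = 2.970; Φ(2.970 − 1.960) = 84.4%. The article states 86%, which is close. The figure takes the outcome as fully observed and makes no allowance for gaps.

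**2. Coverage.** A survey at month s asks about months s − 12 to s. With surveys at s1 and s2:
- gap at the start = max(0, s1 − 12)
- gap in the middle = max(0, s2 − 12 − s1)

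Both are zero only if s1 ≤ 12 and s2 − s1 ≤ 12. The article does not say whether the three-month window is centred (± 1.5 months) or runs up to 3 months late, so both readings are shown.

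| 12-month survey | 24-month survey | Start gap (months) | Middle gap (months) |
|---|---|---|---|
| 12 | 24 | 0 | 0 |
| 13.5 | 24 | 1.5 | 0 |
| 15 | 24 | 3 | 0 |
| 12 | 25.5 | 0 | 1.5 |
| 12 | 27 | 0 | 3 |
| missed | 24 | 12 | – |

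On the centred reading, a 12-month survey at month 10.5 also reaches 1.5 months back before the presentation and could pick up earlier activity.

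**3. Lateness alone.** The article gives no purchase rates, timing or lateness. Assume that a share e = 35 to 65% of 24-month purchases falls in year 1, evenly spread, and that half of the 12-month surveys are L = 1.5 to 3 months late. Share of purchases lost = e × 0.5 × L/12:
- low: 0.35 × 0.5 × 1.5/12 = 2.2%
- high: 0.65 × 0.5 × 3/12 = 8.1%

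**4. Missed 12-month surveys, secondary purchase endpoint.** All rates are assumed: true 24-month purchase 15% (VB) v 5% (UC), a share m answering only at 24 months, and those employers counted as observed throughout. Observed rate = true rate × (1 − m × year-1 share).

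Power = Φ[(d − 1.96 × se0)/se1], with se0 from the pooled rate and se1 from the separate rates. With no loss: se0 = √(0.10 × 0.90 × 2/144) = 0.03536; se1 = √((0.1275 + 0.0475)/144) = 0.03486; power = Φ[(0.10 − 0.0693)/0.03486] = Φ(0.881) = 81.1%.

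| m | Year-1 share VB / UC | Observed VB v UC | Difference (points) | Power |
|---|---|---|---|---|
| 0 | any | 15% v 5% | 10 | 81.1% |
| 10% | 50% / 50% | 14.25% v 4.75% | 9.5 | 78.8% |
| 10% | 60% / 50% | 14.1% v 4.75% | 9.35 | 77.8% |
| 20% | 60% / 60% | 13.2% v 4.4% | 8.8 | 75.3% |
| 20% | 75% / 50% | 12.75% v 4.5% | 8.25 | 70.5% |

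With equal timing in the two arms the ratio of rates stays at 3.0 and only the difference shrinks. The lowest power needs purchases to come earlier in VB than in UC, which is an added assumption.

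**The case against.** **The nominal design is complete.** Surveys exactly at months 12 and 24 cover 0 to 24, so the gap arises only from departures. This is correct, but the protocol permits the departures and provides for contacting non-responders, so they are foreseeable.

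**The scoring rule is not stated.** A reader might infer that a year-1 purchaser who misses the 12-month survey is scored as a non-purchaser. The article does not say so. It says only that all available data are used. An analysis plan that is not shown could treat year 1 as missing or interval-censored. That would limit the bias but would not recover the data. This objection stands, and the undercount is therefore conditional.

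**The direction is not shown.** A reader might also infer that the loss is larger in VB because the presentation is fresh and technical assistance comes early. The section Intervention offers assistance to both arms throughout the 24 months. In VB it consists of building internal support, identifying vendors and developing contracts, all of which come before a purchase. Early concentration in VB is plausible but is not documented.

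**The illustration is narrow.** Its rates appear nowhere in the article, the stated 20% dropout at 24 months is a different quantity from missed 12-month surveys, and the power figures concern a secondary endpoint. No loss is computed for the ordinal primary scale. All of this stands.

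**The survey items were not seen.** The article is condensed and refers to instruments on a project website. These may already ask for dates. If so, the fault lies in the article's sentence and not in the data.

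**Conclusion.** The point holds as a weakness in how the outcome is defined. As worded, the recall rule leaves post-presentation time unasked whenever the first survey is after month 12, the first survey is missed, or the second comes more than 12 months after the first. This follows from the article's text without any assumption.

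The size cannot be derived from the document. Lateness alone costs little: 1.5 to 3 months of recall, or roughly 2 to 8% of purchases under the assumptions above. A missed 12-month survey costs 12 of 24 months and matters more. For the secondary purchase endpoint, with the assumed 15% v 5% and 10 to 20% missed, power falls from 81% to about 71 to 79%, or to 75 to 79% in the scenarios with equal purchase timing in the two arms. These figures also require that employers with only a 24-month survey be counted as observed throughout; otherwise the loss appears as missing data.

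Any effect is probably attenuation of the VB–UC difference. The case for change rests on its low cost and on the fact that later analysis cannot recover months that were never asked about.

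**What to change.** - At the 12-month survey, ask about steps taken since the date of the presentation.
- At the 24-month survey, ask about steps since the last completed survey, or since the presentation if none was completed.
- Record the month and year of any purchase, so that events before the presentation or after month 24 can be set aside.
- Score the highest EBPB level reached over months 0 to 24. This is arguably what a 24-month cumulative incidence already implies, but it should be written down.
- If the instrument already works this way, correct the sentence in Construct Measurement to match.

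The cost is two reworded survey stems and one date item. The change closes the gap in coverage in every case in the table. It has two downsides: employers who missed the 12-month survey face a longer recall, and a replacement representative may not know what happened in year 1, so the longer recall will not recover every early event.

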**Discussion:**

By addressing the 'value to whom?' question, the study advances knowledge about one of the most pivotal problems in the translation of evidence-based care to 'real world' settings: whether purchasers can be influenced to buy healthcare products on the basis of value and not exclusively on the basis of cost. If value-based marketing increases depression product purchase rates over usual care, this study will provide encouragement to market new healthcare products on the basis of the product's value to the purchaser as well as the recipient of care.

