### Scope of Study

The specific aims of the study are: to compare the impact of value-based (VB) and usual-care (UC) intervention on employer purchase of depression products; to identify mediators of intervention impact on employer purchase; and to identify organizational-level moderators of employer purchase.

The first specific aim utilizes an experimental design to study intervention effectiveness. Hypothesis one tests whether VB intervention significantly increases purchasing behavior over UC. The second specific aim utilizes a non-experimental design to study intervention mediators. Hypothesis two tests whether intervention impact on purchasing behavior is mediated by the organization's appraisal of product benefit to the employer more than the employee. Hypothesis three tests whether colleagues influence an organization's appraisal of product benefit to employer. The third specific aim utilizes a non-experimental design to study intervention moderators. Hypothesis four tests whether larger and more mature companies with greater financial latitude demonstrate higher levels of purchasing behavior, as well as companies who make greater investments in their employees and have a higher tolerance for benefit risk, independent of intervention. Hypothesis five tests whether companies with de-centralized onsite purchasing groups in which the presentation participant has primary influence will demonstrate higher levels of purchasing behavior, independent of intervention. Hypothesis six tests whether companies with strong vendor relationships demonstrate higher levels of purchasing behavior, independent of intervention.

Before initiating the study, the research team: fully articulated a conceptual framework; pilot tested the VB intervention prototype to demonstrate intervention feasibility, to collect/integrate employer feedback to further strengthen the intervention, and to estimate effect size; created instrumentation to measure intervention mediators, moderators, and outcomes with demonstrated reliability and validity; investigated business coalition interest in participating in the study; and received approval from the Florida State University Institutional Review Board.

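### The tested outcome and its analysis do not match: the abstract and aim 1 name product purchase, the Methods point to the four-level EBPB scale, and the stated cumulative incidence analysis does not fit that scale or its power statement

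*Protocol article*

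**What the plan says.** Purchase is the outcome in two places. The abstract's Methods paragraph says the team will "evaluate intervention impact on the purchase of depression products using a cumulative incidence analysis of 12- and 24-month data". In Scope of Study, the first specific aim is "to compare the impact of value-based (VB) and usual-care (UC) intervention on employer purchase of depression products".

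The EBPB scale is the outcome in three places:
- Scope of Study, under that same aim: "Hypothesis one tests whether VB intervention significantly increases purchasing behavior over UC".
- Construct Measurement defines employer benefit purchasing behavior over the previous 12 months, which "will be measured at 12 and 24 months as an ordinal variable with four levels". The levels run from exposure only, through discussion and pursuit, to purchase. The section adds: "Planned secondary analyses will examine intervention impact on product purchase defined as a dichotomous variable".
- Data Analysis says that "the post-attrition sample will provide 86% power to find a 0.35 effect size on the EBPB scale", with a two-tailed 5% test, 20% dropout and 144 per group.

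Data Analysis also names the method for the experimental hypothesis: "conducting a cumulative incidence analysis over 24 months". It does not say which outcome this covers.

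The abstract's Discussion frames its conclusion on purchase: "If value-based marketing increases depression product purchase rates over usual care". The main Discussion likewise says the trial will determine whether the intervention can raise product purchase.

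**The concern.** Cumulative incidence describes the proportion of units that have had a defined event by a given time. The only event the article links to it is purchase, in the abstract, and the Methods put purchase as a yes/no variable among the secondary analyses. Nothing says how the method would apply to a four-level scale recorded separately for each 12-month window. The named analysis therefore fits neither the scale nor the effect size on which power is stated.

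Two things are at stake. A reader of the abstract expects a test of purchase with 86% power, although that figure belongs to a different variable. And movement on EBPB can come from more discussion or pursuit as well as from more purchases, so a positive EBPB result is not in itself evidence that purchase rates rose, which is what both discussion sections are about.

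**Working it through.** **Step 1. The outcome, place by place**

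| Place | Outcome | Analysis |
|---|---|---|
| Abstract, Methods | purchase | cumulative incidence, 12- and 24-month data |
| Scope of Study, aim 1 | purchase | not stated |
| Scope of Study, hypothesis one | purchasing behavior | not stated |
| Construct Measurement | EBPB, four levels; yes/no purchase secondary | not stated |
| Data Analysis, method | experimental hypothesis | cumulative incidence over 24 months |
| Data Analysis, power | EBPB | 0.35 effect size |
| Abstract, Discussion | purchase rates | not stated |

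Purchase is the top level of EBPB. The two outcomes are related but are not the same endpoint.

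**Step 2. The plan's own figure**

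Inputs: 360 employers (abstract), 1:1 within pairs (Randomization), 20% dropout, effect size 0.35, two-sided 5% (Data Analysis).

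- Evaluable per group: 360 × 0.8 / 2 = 144, as stated.
- Reading 0.35 as a standardised mean difference d, power = Φ(d·√(n/2) − 1.96) = Φ(0.35 × √72 − 1.96) = Φ(2.970 − 1.960) = Φ(1.010) = 84.4%. The t-test version gives 84.1%.

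This is within 2 points of 86%. The power statement is consistent with a comparison of EBPB scores. The article says effect size without the word standardised; that reading is inferred from this agreement.

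**Step 3. The same sample with purchase as the outcome**

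The article gives no purchase rates, so the usual-care (UC) rate p₁ is assumed. With p̄ the mean of p₁ and the value-based (VB) rate p₂, and n = 144:

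power = Φ{[(p₂ − p₁) − 1.96·√(2p̄(1 − p̄)/n)] / √([p₁(1 − p₁) + p₂(1 − p₂)]/n)}

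For 10% v 20%: p̄ = 0.15, the null standard error is 0.0421 and the alternative 0.0417. Power = Φ[(0.10 − 1.96 × 0.0421)/0.0417] = Φ(0.42) = 66%.

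Solving for p₂:

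| Assumed UC rate | VB rate for 80% power | VB rate for 86% power |
|---|---|---|
| 5% | 14.8% | 15.9% |
| 10% | 22.1% | 23.3% |
| 20% | 34.7% | 36.0% |

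**Step 4. What a 0.35 effect on EBPB could mean for purchase**

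Score the levels 1 to 4 and assume a UC split of 80/10/5/5%, which has mean 1.35 and variance 0.6275.

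- *All movement into discussion only.* VB 52/38/5/5% has mean 1.63 and variance 0.6331. Then d = 0.28/√0.6303 = 0.353, with purchase 5% in both groups.
- *Proportional-odds shift.* An odds ratio of about 2.27 gives d = 0.35 and moves purchase from 5% to about 10.7%. Power for yes/no purchase is then about 43%.

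The first case is an extreme and the second more moderate. In neither does the 86% apply to purchase.

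**The case against.** The strongest reply is that the Methods do settle the outcome. Hypothesis one speaks of purchasing behavior, Construct Measurement defines that term as the four-level scale and calls yes/no purchase secondary, and the power statement is confined to EBPB. On this view only the abstract, aim 1 and the term cumulative incidence are out of line. That largely stands, and it is why EBPB is the natural choice for the primary outcome. A reader might infer that the team is free to choose its headline test once the data are in. The article does not support that: promoting purchase would contradict a published label. Nor does the article use the word primary; EBPB's role is inferred.

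Cumulative incidence may also be meant loosely, as the level reached by 24 months when the two 12-month windows are combined, with the model left to a fuller document. That is possible, but the article does not say so, and the abstract ties the term to purchase. Condensing explains missing detail, not differing statements of which outcome is tested.

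A reader might also infer that the article plans to claim more purchasing from a positive EBPB result. It does not: the abstract's Discussion makes its conclusion conditional on purchase rates themselves. The case in which EBPB shifts with no extra purchase is possible but rests on an assumed extreme split. Finally, the 86% is not wrong, and the article never claims it for purchase.

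**Conclusion.** The inconsistency is in the stated text. The abstract and aim 1 name an outcome that the Methods make secondary. Within Data Analysis, the method named for the experimental hypothesis suits a yes/no event, while the power statement suits a comparison of scores.

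The 86% holds within tolerance (about 84%) for EBPB means with 144 per group. It does not carry over to purchase, where 80% power needs increases of about 10, 12 and 15 percentage points from assumed UC rates of 5%, 10% and 20% (14.8 − 5 = 9.8; 22.1 − 10 = 12.1; 34.7 − 20 = 14.7). These figures rest on the assumed UC rates, a simple two-proportion comparison and the 20% dropout in the plan.

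The sample size need not change on this account. What has to be settled is which outcome is primary, which test goes with it, and what a positive result may be said to show.

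**What to change.** 1. Name one primary outcome with a matching test. On the Methods' own labels this is EBPB over 24 months, with a stated rule for combining the 12- and 24-month reports. Analyse it by an ordinal or mean-score comparison consistent with the power statement. A proportional-odds model is one option; if it is used, restate the power for it.
2. Assign the cumulative incidence analysis explicitly to the secondary yes/no purchase outcome. State its detectable difference with the usual-care rate assumed.
3. Align the abstract and aim 1 with hypothesis one and Construct Measurement.
4. Base any conclusion that value-based marketing increases purchase, in the abstract's Discussion and the main Discussion, on the purchase analysis.

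Making purchase primary would also remove the conflict, provided its lower power is disclosed.

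The cost is wording in the protocol and analysis plan, with no change to recruitment or data collection. The downside is a narrower claim: a positive EBPB result would show movement along the purchasing process, not by itself more purchases.
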